## Abstract

**Objective::**

To assess the effect of the program of individualized diabetes education on type 2 diabetes mellitus (DM) patients.

**Methods::**

This is a single-center randomized controlled trial that will be implemented from December 2020 to April 2021. The experiment was granted through the Research Ethics Committee of People's Hospital of Chengyang District (03982765). Patients are randomly assigned to the study group and control group with 50 cases in each group. Patients who meet the following criteria will be included in our study: patients diagnosed with type 2 DM based on the World Health Organization diagnostic criteria in 1999; patients who can take part in the follow-up researches after discharge; patients who can provide the written informed consent. And the exclusion criteria include: the known mental or psychological disorders, for instance, severe anxiety disorders or depression; severe comorbidities, e.g. liver dysfunction, kidney failure, stroke, and cancer; Uncontrolled diabetes complications, for instance, infection, acidosis, as well as peripheral vascular disease. The clinical examination shall be conducted during each follow-up period, and the laboratory examination is implemented as necessary in the process of each hospital visit. At the end of the 6-month study, each patient's blood pressure, waist circumference, body mass index, blood lipids, as well as fasting blood glucose are evaluated.

**Results::**

Table 1 reveals the comparison of biochemical results and clinical results between the control group and the study group.

**Conclusion::**

Individualized diabetes education may improve the clinical outcomes in patients with type 2 DM.

**Trial registration::**

The protocol was registered in Research Registry (researchregistry6232).

## Introduction

1

Diabetes mellitus (DM) is a leading cause of mortality worldwide.^[1,2]^ It is a kind of debilitating and complex disease that, if not properly controlled, can lead to serious and substantial negative health consequences.^[3]^ On the basis of World Health Organization, the type 2 DM is caused by the body's ineffective use of insulin. Currently, the prevalence of type 2 DM is a major national and global health problem. Type 2 DM accounts for 90% of all the cases of diabetes, and the forecasts for the future seem grim, as the number of diabetics worldwide is expected to increase to 552 million, along with increased complications and health-care costs.^[4]^ Although the increased availability of guidelines of evidence-based treatment and anti-hypoglycemic medications, the percentage of type 2 DM patients who fail to meet their blood glucose targets is still on the rise.^[5,6]^ One of the main reasons is the delay of intensive treatment despite poor glycemic control, which is known as therapeutic or clinical inertia.^[7]^ An analysis of DM patients who adhered to diet therapy indicated that only 20 to 40% followed their diet guidelines.

Because of the complex etiology of long-term complications of type 2 DM and the existence of a range of changeable risk factors, multifactorial treatment is often required.^[8,9]^ There are several factors that affect compliance with prescribed treatment, containing knowledge levels, the environment, habits as well as attitudes.^[10,11]^ At present, most programs of diabetes education are knowledge-based, emphasizing self-care, lifestyle change, and the active participation in the management of disease.^[12,13]^ These educational programs are usually targeted at a group of patients. There is a lack of information about the impact of personality and individualized diabetes education on the outcomes of type 2 DM management. Hence, we carry out this randomized controlled research protocol to assess the effect of the program of individualized diabetes education on type 2 DM patients.

## Methods

2

### Study design

2.1

This is a randomized controlled and single-center study that will be implemented from December 2020 to April 2021. The experiment was granted through the Research Ethics Committee of People's Hospital of Chengyang District (03982765) and registered in Research Registry (researchregistry6232).

### Patients and randomization

2.2

Patients are randomly assigned to the study group and control group with 50 cases in each group. Patients who meet the following criteria will be included in our study: patients diagnosed with type 2 DM based on the World Health Organization diagnostic criteria in 1999; patients who can take part in the follow-up researches after discharge; patients who can provide the written informed consent. And the exclusion criteria include: the known mental or psychological disorders, for instance, severe anxiety disorders or depression; severe comorbidities, e.g., liver dysfunction, kidney failure, stroke and cancer; uncontrolled diabetes complications, for instance, infection, acidosis, as well as peripheral vascular disease.

### Interventions

2.3

Individualized education is provided to the study group patients by face-to-face counseling over 1 hour, based on the personality of the patient. The patient's knowledge on diabetes and self-care is assessed, and a tailored self-care plan is provided to each patient after the counseling. These plans are jointly developed by the nursing educators and a clinical psychologist in our hospital, covering dietary modification, exercises programs, adherence to medications, self-monitoring of blood glucose and blood pressure, and psychological counseling.

Education focuses on the significance of self-care programs and guiding patients to adhere to medications. A detailed explanation of the pathogenesis of diabetes, role of medications, and the use of self-monitoring equipment are provided to address patient's concerns and queries. The family members of patients are encouraged to help monitor the medication compliance. After discharge, all the patients are followed up in our outpatient department for 6 months at the end of each calendar month. All the patients are invited to participate in a 3-monthly forum held in our hospital's educational facilities. On the forum, patients are encouraged to exchange their ideas and views on the self-care of diabetes and share their progress in managing diabetes. In control group, patients receive face-to-face education for an hour in a group during their hospitalization. These educational courses are implemented via a same group of nurses who provided educational courses for study group. The main contents of education involve the basic knowledge of diabetes, the compliance and proper use of antidiabetic medications, the changes of lifestyle and diet, and the self-monitoring of the levels of blood glucose. Personality evaluation is not conducted and the plan of personalized self-care is not offered.

### Assessment of outcomes

2.4

The clinical examination shall be conducted during each follow-up period, and the laboratory examination is implemented as necessary in the process of each hospital visits. At the end of the 6-month study, each patient's blood pressure, waist circumference, body mass index, blood lipids, as well as fasting blood glucose are evaluated.

### Statistical analysis

2.5

The analysis of all data can be carried out with the software of IBM SPSS Statistics for Windows, version 20. Subsequently, all data can be represented with proper features, for example, median, mean, percentage, and the standard deviation. For each group, their corresponding qualitative parameters are assessed through the *t* test. And χ^2^ tests are applied for the determination of categorical variables. When *P* is less than .05, it is considered to be significant in statistics.

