## Results

3

Table 1 reveals the comparison of biochemical results and clinical results between the control group and the study group.

**Table 1 T1:** The comparison of biochemical results and clinical results between the control group and the study group.

Parameter	Intervention group (n = 50)	Control group (n = 50)	*P* value
Waist circumference			
Body mass index			
Systolic blood pressure			
Diastolic blood pressure			
Fasting blood glucose			
Triglyceride			
Low density lipoprotein			
High-density lipoprotein			
Glycosylated hemoglobin			

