## Conclusion

5

Individualized diabetes education may improve the clinical outcomes in patients with type 2 DM.

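### No outcome is named primary and all nine Table 1 comparisons share one unadjusted P < .05 threshold, so any single favourable result could be presented as support for a conclusion about the outcomes collectively

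*Protocol article*

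**What the plan says.** The objective in the Introduction is "to assess the effect of the program of individualized diabetes education on type 2 DM patients"; it names no endpoint.

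Section 2.4 lists what is measured at the end of the study, without ranking: "blood pressure, waist circumference, body mass index, blood lipids, as well as fasting blood glucose are evaluated".

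Section 2.5 describes the tests ("their corresponding qualitative parameters are assessed through the" *t* test, with χ² tests for categorical variables) and gives a single significance rule: when P "is less than .05, it is considered to be significant in statistics". It contains no hierarchy and no adjustment for the number of comparisons.

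Table 1 in section 3, which is to show "the comparison of biochemical results and clinical results between the control group and the study group", has nine empty rows and a P value column: waist circumference, BMI, systolic pressure, diastolic pressure, fasting glucose, triglyceride, LDL, HDL and HbA1c. The last of these ("Glycosylated hemoglobin") is not in the section 2.4 list.

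Section 5, like the Abstract, concludes: "Individualized diabetes education may improve the clinical outcomes in patients with type 2 DM".

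**The concern.** The trial asks one general question and plans nine separate tests, any of which may be called significant at .05. Nothing says which test answers the question, or how many favourable results are needed and on which outcomes. The conclusion is worded about the outcomes as a group, so one favourable row among nine could be put forward as supporting it, and no single row could count against it. The sample size does not settle the matter either: section 2.2 says "Patients are randomly assigned to the study group and control group with 50 cases in each group" and ties that number to no outcome.

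The list of outcomes is itself not settled. Section 2.4 implies eight of the Table 1 rows and Table 1 has nine. At stake is how far a significant P value from this trial can be trusted as evidence that the programme works.

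**Working it through.** The document states no trial-wide error rate, so there is no figure of its own to reproduce. The check asks what following the plan as written would produce if the programme had no effect on any outcome.

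**Inputs from the protocol article**
- Threshold per test: .05 (section 2.5).
- Number of tests: 9 (Table 1), or 8 if only the outcomes implied by section 2.4 are counted: two pressures, waist, BMI, three lipids and fasting glucose.
- Group size: 50 per arm (section 2.2).

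**Assumptions, because the document does not give them**
- Tests are two-sided, so each has a .025 chance of a falsely favourable result.
- Correlations between outcomes are unknown. Three paired patterns and several uniform values were tried, with each statistic oriented so that a positive value means improvement.

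| Paired pattern | Waist-BMI | Systolic-diastolic | Fasting glucose-HbA1c | Triglyceride-HDL | All other pairs |
|---|---|---|---|---|---|
| Low | 0.7 | 0.5 | 0.6 | 0.3 | 0 |
| Middle | 0.8 | 0.6 | 0.7 | 0.4 | 0.15 |
| High | 0.9 | 0.7 | 0.8 | 0.5 | 0.3 |

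**Independent outcomes, k tests**
- Either direction: 1 − (1 − .05)^k. For k = 9: 1 − 0.95^9 = 0.370. For k = 8: 1 − 0.95^8 = 0.337.
- Favourable direction only: 1 − (1 − .025)^k. For k = 9: 1 − 0.975^9 = 0.204. For k = 8: 1 − 0.975^8 = 0.183.

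**Correlated outcomes**, by simulating nine multivariate normal statistics (400,000 draws per scenario):

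| Scenario | At least one P < .05, either direction | At least one P < .05, favourable |
|---|---|---|
| Nine independent | 37.0% | 20.4% |
| Eight independent (section 2.4) | 33.7% | 18.3% |
| Paired, low | 34.7% | 18.8% |
| Paired, middle | 32.8% | 17.0% |
| Paired, high | 29.4% | 14.8% |
| Uniform 0.3 | 32.5% | 16.5% |
| Uniform 0.5 | 26.8% | 13.3% |
| Uniform 0.8 | 16.6% | 8.3% |

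Simulated two-sample *t* tests with 50 per arm (40,000 trials per paired pattern) agree: 35.0%, 32.9% and 29.0% for either direction, and 19.0%, 17.0% and 14.7% for favourable results only.

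The nominal favourable rate for one two-sided test at .05 is 2.5%. Under independence the ratio is 20.4 / 2.5 = 8.2. At about 15%, the lower end of the paired range, it is 15 / 2.5 = 6.

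**The case against.** Four points can be made for the plan.

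1. *No success rule is broken, because none is stated.* A reader might infer that the trial will be declared successful if any of the nine tests is significant. The document does not say so. It gives a per-comparison threshold, claims no trial-wide error rate, and offers a conclusion hedged with the word may. This stands: the any-of-nine criterion is a reading of what the plan permits, not something that the plan prescribes.

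2. *One false positive in three overstates the harm.* A reader might take the 37.0% as the chance of wrongly claiming benefit. It counts significant worsening as well, which would not support the conclusion. This also stands, and the favourable-only rate is the relevant one for a false claim of benefit.

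3. *The correlations are invented.* They are assumptions, which is why a range is shown. Strong uniform correlation lowers the figures considerably, but a value such as 0.8 across waist, pressures, lipids and glucose together is implausible. Even there the favourable rate is 8.3%.

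4. *An unseen analysis plan may deal with multiplicity.* The absence of an adjustment method could be answered that way and is not the point here. Naming the primary outcome is a protocol matter. The article is also not merely silent: it has its own outcomes and statistics sections, and they fix an unranked list and one threshold for all of it.

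**Conclusion.** The point holds in this form: no outcome is named primary, nine comparisons share one unadjusted .05 threshold, and nothing links the collective conclusion to those tests. A single favourable result on any row could be presented as support.

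If the programme had no effect, at least one falsely favourable result would be expected in about 15-19% of such trials under the assumed paired correlations, and in 20.4% if the outcomes were independent. For a significant result in either direction the corresponding figures are about 29-35% and 37.0%, with 26.8% at a uniform correlation of 0.5. All of these rest on two-sided tests, and all but the independence figures rest on correlations that the document does not supply.

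The document does not support saying that success is formally judged on any one of nine tests, that a stated 5% trial-wide rate is violated, or that an ineffective programme would appear beneficial one time in three.

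The point still needs action, because it decides what the trial may conclude, and a primary outcome chosen after the results are seen would not prevent selection.

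**What to change.** Before outcome data are examined, and in the registry entry as well as the protocol:

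- **Name one primary outcome**, measured in all patients at 6 months, with the between-group difference tested two-sided at .05. The choice belongs to the investigators. HbA1c is a natural candidate only if section 2.4 is amended to list it among the 6-month evaluations. Otherwise choose an outcome already listed there, such as fasting blood glucose. Settle this in advance; do not let it depend on which measurements turn out to be available.
- **Make the remaining rows of Table 1 secondary.** Either test them with Holm's procedure, or report estimates with 95% confidence intervals and make no significance claim.
- **Make the conclusion conditional on the primary result**, in both the Abstract and section 5.

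With one primary test the chance of a falsely significant primary result returns to 5%, of which 2.5% is in the favourable direction.

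The cost is wording, plus ensuring that HbA1c is measured in every patient at 6 months if it is chosen. The statistical downside is a stricter threshold for the eight secondary outcomes under Holm, with a first step of .05/8 = .00625. Reporting them as estimates only avoids that.

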## Results

3

Table 1 reveals the comparison of biochemical results and clinical results between the control group and the study group.

**Table 1 T1:** The comparison of biochemical results and clinical results between the control group and the study group.

Parameter	Intervention group (n = 50)	Control group (n = 50)	*P* value
Waist circumference			
Body mass index			
Systolic blood pressure			
Diastolic blood pressure			
Fasting blood glucose			
Triglyceride			
Low density lipoprotein			
High-density lipoprotein			
Glycosylated hemoglobin			

## Discussion

4

Some articles have suggested that the education of type 2 DM patients is related to the improvement of prognosis, which may be multifaceted.^[14–16]^ Individualized counseling or education, as well as a written plan of self-care on the basis of patient's personality, may improve patients’ motivation in adhering to dietary and life style modification measures.^[17]^ This is supported via significant reductions in waist circumference, body mass index, and body weight, which are known to help diabetics control blood pressure, cholesterol, and blood sugar.^[17]^ Moreover, a recent research suggested that the knowledge of diabetes was closely related to good control of blood glucose and medication adherence.^[18]^ Despite the patients’ medication compliance is not evaluated in our current study, self-care programs and individualized education may improve the patients’ compliance with cardiovascular and hypoglycemia medications, so as to better control blood lipids, blood pressure, and blood glucose. Although the psychologists are involved in the project, there are no psychosocial results as endpoints. This may be a weakness in research design and in-depth researches are needed.

## Conclusion

5

Individualized diabetes education may improve the clinical outcomes in patients with type 2 DM.
